**Fig. 1 Fig1:**
[figure not shown]
Map of the study areas (Map generated using the tmap package in R version 3.6.1 using base maps from the GADM database of Global Administrative Areas, version 2.8. URL: www.gadm.org)

### Eligibility criteria

The provinces included in the trial have been selected based on the presence of malaria volunteer network in the province, capacity of implementing partners for field implementation, high malaria burden and high MMP activities.

Villages/worksites managed by the implementing partner in the selected provinces will be screened against the following exclusion criteria by investigators and implementing partner staff. A village/worksite will be excluded from the study if it: (1) has no malaria cases or annual parasite incidence less than 1 in any of the past three years (2018–2020), (2) has no MMPs, (3) has no malaria volunteer actively working in the village/worksite, (4) has a government health facility for malaria services, or (5) has another malaria volunteer program operated by any organizations other than implementing partner.

After the village/worksite has been selected, the MMPs with the following criteria will be included in the study for receiving the intervention (i.e. personal protection package): (1) currently living in the selected villages/worksites, and (2) being any of the following types of workers—traditional slash-and-burn and paddy field farming communities visiting their forest farms (commonly ethnic minority groups), seasonal agricultural laborers, forest workers in the informal sector (hunters, small-scale gem/gold miners, people gathering forest products (precious timber, construction timber, rattan/bamboo), transient or mobile camp residents associated with commercial projects (road/pipeline construction, large-scale logging, deep seaport projects, etc.), and formal and informal cross-border migrant workers.

### Study design and sample

The study design for the trial component of this study is an open stepped-wedge cluster-randomised controlled trial, randomised at the village/worksite level and conducted over a 12-month period, following a one-month baseline period (Fig. 2). The study will be implemented between March 2022 and February 2023. The personal protection package for MMPs will be implemented sequentially in a minimum of 488 villages serviced by approximately 488 Village Malaria Workers (~ 428 in Lao PDR and ~ 60 in Cambodia). Villages from each country will be randomised into 11 blocks, with blocks transitioned in random order from control (no personal protection package) to intervention (with personal protection package) states at monthly intervals (10 blocks of 44 villages for the first 10 steps and a block of 48 villages transitioned at the final step). All eligible MMPs in participating villages will receive the intervention during the study, but the month at which they transition from a control to the intervention state will be randomised.

**Fig. 2 Fig2:**
[figure not shown]
Timeline for stepwise implementation of the personal protection package in the selected villages

### Study power

It is estimated that approximately 11 RDTs per month will be undertaken at each study site (village/worksite), yielding an approximate total of 64,416 RDT tests over 12 months. Given this sample size, the trial will be able to detect a minimum relative reduction of 34% in the odds (OR = 0.66) of RDT-detectable malaria infection attributable to the intervention (assuming a village intraclass correlation [ICC] = 0.42 [16]; 5% significance; 90% power and 1% RDT malaria prevalence). Power estimation was based on estimation of an intervention effect using trial data from a stepped-wedge cluster-randomised design assuming analysis by generalized linear mixed modelling (GLMM).

### Data analysis

Data entry will be managed in a REDCap database developed by Burnet Institute. For the stepped-wedged cluster-randomised trial, both descriptive and primary outcome trial analyses will be performed. To assess the effectiveness of distribution of the personal protection package, difference in the prevalence of malaria infection will be estimated across intervention and control periods using GLMM (logit link function and binomial distribution) with time-varying fixed factors for intervention status and time, and crossed random effects for village and time implemented to account for the dependencies inherent in the data given the stepped-wedge design. We will also explore any village-specific heterogeneity in effect by specifying a random effect for the intervention and the extent to which effectiveness of intervention is time-dependent. GLMM will be extended to include model terms for country (main and interaction effects), and these will used to assess the extent of country-specific heterogeneity in intervention effect. Analyses of secondary outcomes will also involve multi-level modelling (i.e., linear mixed modelling (LMM) and GLMM). Statistical analysis will be performed using Stata version 17.

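### The stated primary model leaves out each site's 2018–2020 malaria incidence, a pre-randomisation covariate that would give a modest gain in precision

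*Protocol article*

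**What the plan says.** All references are to the protocol article.

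- **Data analysis.** The primary model is a logistic mixed model for RDT positivity "with time-varying fixed factors for intervention status and time, and crossed random effects for village and time". The further terms named are a random intervention effect, time-dependence of the effect, and country with its interaction. Prior village incidence is not among them.
- **Eligibility criteria.** A site is excluded if it "has no malaria cases or annual parasite incidence less than 1 in any of the past three years (2018–2020").
- **Study design and sample.** "Villages from each country will be randomised into 11 blocks", in sequences given as "10 blocks of 44 villages for the first 10 steps and a block of 48 villages transitioned at the final step". Country is the only factor mentioned in the allocation.
- **Study power.** The inputs are "approximately 11 RDTs per month will be undertaken at each study site (village/worksite"), "yielding an approximate total of 64,416 RDT tests over 12 months", a village ICC of 0.42, 1% RDT prevalence, 5% significance, 90% power and an odds ratio of 0.66.
- **Discussion.** The authors note that the design draws on comparisons between villages as well as within them.

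**The concern.** The exclusion criterion can be applied only by someone who knows each candidate site's cases and API for three years. The trial team should therefore hold a measure of burden, fixed before randomisation, for every cluster. The model as written does not use it.

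The village random effect does not make such a covariate redundant. Part of the information on the intervention comes from comparing treated and untreated villages in the same month. With a large assumed ICC and few positives per village, the random effect recovers each village's level only in part, and what it misses adds noise to that comparison. A covariate that predicts the level removes some of this noise. It leaves the target unchanged, because the model already estimates an odds ratio conditional on village. What is at stake is the width of the confidence interval.

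**Working it through.** **1. Reproduce the plan's figure.** 488 villages × 11 tests × 12 months = 64,416, exactly as stated.

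**2. Between-village variance.** The article does not give the scale of the ICC. I read it on the logit scale: 0.42/(1 − 0.42) × π²/3 = 0.724 × 3.29 = 2.38, an SD of 1.54.

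**3. Data per village.** 11 × 12 = 132 tests, and 132 × 0.01 = 1.32 expected positives. The article does not say which prevalence the 1% describes. The share of villages with no positive all year depends on the reading:
- 61% if 1% is the control-period average
- 57% if 1% is the whole-trial average
- 38% if 1% is the prevalence in the median village

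**4. What the random effect learns.** With 1% as the control-period average, a village with no positive test moves from a prior mean of 0 (SD 1.54) to a posterior mean of about −0.76 (SD about 1.22). Under the two average readings, the trial data recover about 51–54% of the between-village variance across all villages. The level is learned in part, not fully.

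**5. Gain from the covariate.** I used the expected information of a logistic random-intercept model with 12 categorical months, 11 sequences (10 of 44 villages and one of 48), 11 tests per village-month and OR 0.66. A covariate explaining a share R² of the village variance leaves (1 − R²) × 2.38 unexplained.
- Variance reduction = 1 − (SE adjusted / SE unadjusted)²
- Power = Φ(|ln 0.66|/SE − 1.96), with |ln 0.66| = 0.4155
- Example without the covariate: 0.4155/0.1435 − 1.96 = 0.94, giving 82.5%

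| Assumed R² | 1% = control period: SE; reduction; power | 1% = whole trial: SE; reduction; power | 1% = median village: reduction; power |
|---|---|---|---|
| 0 | 0.1435; –; 82.5% | 0.1333; –; 87.7% | –; 99.5% |
| 0.10 | 0.1434; 0.1%; 82.6% | not run | 0.5%; 99.5% |
| 0.25 | 0.1426; 1.4%; 83.0% | 0.1325; 1.2%; 88.0% | 1.6%; 99.6% |
| 0.50 | 0.1399; 4.9%; 84.4% | 0.1294; 5.7%; 89.4% | 3.2%; 99.6% |
| 0.75 | 0.1344; 12.3%; 87.1% | 0.1247; 12.5%; 91.5% | 8.6%; 99.7% |

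Reductions come from unrounded SEs, so the last digit may differ from what the table's SEs give.

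**6. Cross-checks, with 1% as the control-period average.** A separate information calculation gave reductions of about 0.5%, 2.4%, 7% and 13% at R² of 0.10, 0.25, 0.50 and 0.75. Fitting the model to 77 simulated trials gave a mean SE of 0.1457 unadjusted, and 0.1432, 0.1410 and 0.1371 at R² of 0.3, 0.5 and 0.7, which is about 3%, 6% and 11%. Taken together, the results under the average-prevalence readings are roughly 0–2% at R² 0.10–0.25, 5–7% at 0.50 and 12–13% at 0.75.

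**The case against.** **Scope.** The article is condensed, and a covariate list may sit in an analysis plan that is not shown. A stepped-wedge mixed model without covariates is standard and valid. This stands in part. Silence cannot be read as a decision never to adjust. But the section sets out the primary model and its extensions term by term, so a suggestion about that stated model is fair.

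**Size.** The gain is small and rests on an R² that the documents do not give. This stands. At R² 0.50 the SE moves from 0.1435 to 0.1399, about 2.5%, and power rises by less than 2 points. There are reasons to expect a low R²:
- Screening removes low-incidence sites, which truncates the covariate.
- The data are more than a year old at the March 2022 start.
- API counts cases per population, whereas the outcome is positivity among people tested.
- Some sites are worksites with moving populations.

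**Availability.** Screening needs only a threshold decision, so a numeric API may not have been kept for every site. Dropping such sites would conflict with the Discussion's commitment to use all data in the primary analysis. This stands, and the fix has to deal with it.

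**Stronger readings that a reader might infer.**
- That villages without positives tell the random effect nothing. Step 4 shows that they do inform it.
- That most villages certainly have no positive. This holds only if 1% is an average prevalence. That is the more natural reading, since the median-village reading gives 99.5% power, far from the stated 90%, but the article does not settle it.
- That the stated power is wrong. The re-derived values run from 82.5% to 99.5% across readings, and 90% lies inside that range.
- That allocation should have been stratified by incidence. Cambodia has about 60 villages over 11 blocks, or about 5.5 per block, which is thin for further strata. The article appeared in September 2022, after the planned start, so allocation has probably been drawn.

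**Conclusion.** The point holds as a modest, nearly free improvement. The stated primary model omits a pre-randomisation measure of village burden that the eligibility screen requires, and the trial's own data recover only about half of what that measure might predict. If 1% is an average prevalence, the variance of the log odds ratio would fall by roughly 0–2% when API explains 10–25% of the between-village logit variance, 5–7% at 50% and 12–13% at 75%. If 1% is the median-village prevalence, the gain is smaller: 3.2% at 50% and 8.6% at 75%.

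The figures rest on assumptions: the R² values themselves, an ICC on the logit scale, a two-sided 5% test, a common intervention effect, and no random time variation beyond the fixed month effects. The documents show no bias in the planned analysis and no error in the stated power.

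**What to change.** In Data analysis, pre-specify the site's log mean API for 2018–2020 as a fixed covariate in the primary model, before outcome data are analysed. The logarithm is defined for every included site with a value. On either reading of the exclusion rule, at least one year has an API of 1 or more, so the three-year mean is at least 1/3.

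State in the same place that a site without a numeric value is kept, by a missing indicator or simple imputation, so that no village is dropped. Keep the unadjusted model as a sensitivity analysis.

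The cost is a sentence or two of text, retrieval of the screening figures, and one parameter (two with a missing indicator). If API turns out to predict little, almost nothing is lost. The value depends on pre-specification: added after results are seen, the adjustment would look selective.

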**Methods:**

A personal protection package consisting of long-lasting insecticidal hammock net, insect repellent and health communication pamphlet was developed in consultation with relevant implementing partners from Cambodia and Lao PDR. An open stepped-wedge cluster-randomised controlled trial will be conducted over a period of 12 months in a minimum of 488 villages (~ 428 in Lao PDR and ~ 60 in Cambodia) to evaluate the effectiveness of the personal protection package. Villages will be randomised into 11 blocks, with blocks transitioned in random order from control to intervention states at monthly intervals, following a 1-month baseline period. The primary outcome of the trial is the prevalence of *Plasmodium* spp. infection diagnosed by rapid diagnostic test. Difference in prevalence of malaria infection will be estimated across intervention and control periods using generalized linear mixed modelling. Nested within the stepped-wedge cluster-randomised controlled trial is a mixed-methods study to explore the acceptability of the personal protection package, feasibility of implementing a personal protection package as a vector control intervention, and knowledge, attitude and practice of MMPs regarding malaria prevention; and cost-analysis to determine the cost-effectiveness of implementing a personal protection package.

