To pragmatically evaluate personal protection packages to reduce malaria in MMPs we chose a stepped-wedge cluster-randomised trial design. There are several advantages to using a stepped-wedge cluster-randomised trial design over a parallel group design (where each cluster is randomised to either an intervention or control condition for the entire duration of the study). In the stepped-wedge design clusters act as their own controls as they experience both the control and intervention conditions during the study period and all clusters ultimately receive the intervention which is important where the intervention is thought to have a largely positive effect and exclusion of study subjects from such benefit might be considered unethical [23]. However, the stepped-wedge design can be susceptible to confounding from time, given it is associated with the monotonic time-varying intervention and may also be associated with the outcome [24–26]. To overcome any potential confounding here, all statistical analyses will be appropriately adjusted for time. Indeed, while overcoming this potential limitation in design, it is also a strength of the stepped-wedge design in that it enables analyses of any temporal effects of the intervention. Furthermore, given the repeated measurements, the effect of the intervention can be estimated using both between- and within-cluster information, and, under certain conditions, this can result in greater statistical power for a given sample size (i.e. smaller standard errors) compared to independent parallel group designs [25, 27].

The proposed study will provide an evidence base for the distribution of tailored personal protection packages for high-risk MMPs in malaria elimination programs in the GMS through established malaria volunteer networks. The pragmatic trial design representing “real-world” distribution of the intervention, together with the nested mixed-methods study which measures essential outcomes for policy adoption of a new tool or strategy will ensure trial findings are translated into National Malaria Guidelines of GMS countries in order to meet national and regional malaria elimination goals.

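### Villages are randomised within country, but the primary model has one time trend for both countries and no country term

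*Protocol article*

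**What the plan says.** Under Study design and sample, the article says "Villages from each country will be randomised into 11 blocks". It gives the country totals as approximate ("428 in Lao PDR and ~ 60 in Cambodia") and the block sizes as "10 blocks of 44 villages for the first 10 steps and a block of 48 villages transitioned at the final step". It does not state the number of villages per country in each block. The abstract describes the same allocation without mentioning country: "Villages will be randomised into 11 blocks, with blocks transitioned in random order from control to intervention states at monthly intervals".

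Under Data analysis, the effectiveness model is a logistic mixed model with "time-varying fixed factors for intervention status and time, and crossed random effects for village and time". Country is brought in afterwards: "GLMM will be extended to include model terms for country (main and interaction effects". These terms are to be "used to assess the extent of country-specific heterogeneity in intervention effect". No country-by-time term is named. The Discussion adds the general commitment that "all statistical analyses will be appropriately adjusted for time".

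**The concern.** Country is the natural stratum of the randomisation, yet the stated primary model does not use it. The fixed time effect is common to both countries. The random time effect is crossed with village, so it is shared too. One calendar trend is enough only if the two countries' trends run parallel on the logit scale, or if country is balanced over crossover dates. The article establishes neither.

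The village random effect takes up most of a constant difference between countries. It cannot take up a difference in how malaria changes over the year. In a stepped-wedge trial, exposure to the intervention rises with calendar time. A trend particular to one country can therefore be partly credited to the intervention if that country's villages cross over earlier or later than average. The Discussion itself names confounding by time as the weakness of the design.

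**Working it through.** **Inputs from the article.** 488 villages (about 428 + 60); blocks of 10 × 44 and 1 × 48; 11 tests per village-month; 12 monthly periods, read as baseline plus 11 steps; ICC 0.42; prevalence 1%; OR 0.66; 5% significance (taken as two-sided); 90% power.

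**Assumed.** The size and shape of any Cambodia-specific trend, for which the article gives no figures.

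**1. Totals.** 488 × 11 × 12 = 64,416 and 10 × 44 + 48 = 488 = 428 + 60. Both agree with the article.

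**2. Stated power.** Generalised least squares for the stepped wedge on the logit scale:
- between-village variance = (0.42/0.58) × π²/3 = 2.38
- variance per village-month = 1/(11 × 0.01 × 0.99) = 9.18
- resulting SE of the log OR = 0.1257
- detectable OR = exp(-(1.960 + 1.282) × 0.1257) = 0.665
- power at OR 0.66 = Φ(0.4155/0.1257 - 1.960) = Φ(1.345) = 91.1%

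This reproduces the stated OR of 0.66 at 90% power, so the same weights are used below. At a mean prevalence of 0.83% over control and intervention periods, the SE is 0.136.

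**3. Country splits that fit the stated block sizes (Lao PDR + Cambodia).**
- A: six blocks of 39 + 5, then four of 38 + 6, last block 42 + 6. Lao PDR 234 + 152 + 42 = 428; Cambodia 30 + 24 + 6 = 60. Cambodian share 11.4%, 13.6% and 12.5%, against 60/488 = 12.3% overall.
- B: five blocks of 38 + 6, then five of 39 + 5, last block 43 + 5. Lao PDR 190 + 195 + 43 = 428; Cambodia 30 + 25 + 5 = 60. Last block 10.4%.
- C: ten blocks of 38 + 6, last block 48 + 0.
- D: ten blocks of 39 + 5, last block 38 + 10.

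A and B are near-balanced. C and D are extreme.

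**4. Shift in the log OR under a shared trend.** The shift is the intervention element of (ΣX′V⁻¹X)⁻¹ ΣX′V⁻¹f. Here f is Cambodia's departure from the shared trend in log odds, and is zero for Lao villages.

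| Split | 2-fold relative fall | 4-fold relative fall | Seasonal, 2-fold (sine) | Seasonal, 2-fold (cosine) |
|---|---|---|---|---|
| A | +0.002 | +0.003 | -0.002 | +0.008 |
| B | -0.003 | -0.005 | +0.002 | -0.009 |
| C | -0.010 | -0.020 | -0.012 | -0.011 |
| D | +0.007 | +0.014 | +0.008 | +0.008 |

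**5. Scale.** For near-balanced splits the largest shift is 0.009/0.126 = 0.07 SE. The largest in the table is 0.020/0.126 = 0.16 SE, which moves an OR of 0.66 to 0.66 × exp(-0.020) = 0.647. Under the null, a shift of 0.16 SE turns a 5% test into Φ(-1.80) + Φ(-2.12) = 5.3%.

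**6. If blocks were drawn without regard to country.** This is how the abstract could be read. Over 1,000 random allocations, the Cambodian count per block has SD 2.1. The 95% limit of the absolute shift is about 0.020 for the four-fold fall and 0.023 to 0.026 for the seasonal patterns.

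**7. With country terms.** A country main effect alone is not enough: in split C it reduces the four-fold shift from -0.020 to -0.011 and leaves the seasonal shifts unchanged. Country-by-month terms remove the shift in every case. The SE rises by at most 0.0001 (split C) and power at OR 0.66 stays at 91.0% or more.

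**The case against.** The best defence is that randomising each country's villages over the blocks is exactly what keeps country nearly unrelated to crossover date, so a shared trend does little harm. That stands, and the near-balanced splits above bear it out.

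Second, the article does address country, through prespecified main and interaction terms, and it promises adjustment for time. The full analysis plan, which is not shown, may already carry the stratum. This stands in part. The parenthesis does not say what country interacts with, but its stated use is heterogeneity of effect, and the primary model as written has no country term. The point concerns terms the article does specify.

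Third, nothing in the article shows that the two countries' trends differ. That stands, and it is why the shifts are conditional.

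A reader might also infer from the block sizes that the last block must have a different country mix. The most even split within each country (38 or 39 Lao and 5 or 6 Cambodian villages) gives blocks of 43 to 45, never 48. The article does not support that inference. Splits such as 48 + 0 or 38 + 10 follow only if the first ten blocks are identical, which is nowhere stated, and split A keeps the last block at 12.5% Cambodian. The country counts are approximate and the total is a minimum, so exact block arithmetic carries little weight. The block sizes need no change.

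**Conclusion.** The point holds as a minor one. The stated primary model does not use the country stratum of the randomisation and imposes one time trend on both countries. If the trends differ, chance imbalance of country over crossover dates shifts the log OR by under about 0.01 for near-balanced blocks and up to about 0.02 for unbalanced ones, against an SE of about 0.126. This would not change the trial's conclusion except at the margin. A reader might infer a material bias or an inflated type I error; the figures do not support that, since the worst tabulated case takes a 5% test to about 5.3%.

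The sizes rest on assumed trends (relative falls of two- to four-fold, or a two-fold seasonal amplitude) and on a linear working model with equal weight per village. The reason to act is that the correction costs almost nothing.

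**What to change.** In Data analysis, or in the analysis plan if it does not already say so, specify country-by-month fixed effects in the primary model in place of the single time factor. Keep the intervention-by-country term for the heterogeneity analysis, added to that same model, so that it is not left to absorb a difference in trend. It would also help to report the number of villages per country in each block.

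The cost is a change of wording and about 12 more parameters, with some 64,000 tests. The standard error and power are essentially unchanged. The allocation and the block sizes stay as they are.
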